### Plans to give access to the full protocol, participant-level data, and statistical code {31c}

All study data including study protocol, statistical analysis plan, informed consent form, and clinical study report can be shared when a proper agreement is formed according to the European Union GDPR protection statement.

## Oversight and monitoring

### Composition of the coordinating centre and trial steering committee {5d}

The project is coordinated and run day to day in collaboration with each urological research unit, the Department of Urology, and the Department of Diagnostic Radiology at the respective centres. PIs at each centre will monitor correct data collection following the ICH GCP guidelines.

### Composition of the data monitoring committee, its role and reporting structure {21a}

The data monitoring is done by the research team at the Urological Research Unit at Rigshospitalet and Herlev and Gentofte University Hospital. As part of the Urological Research Unit at Rigshospitalet and Herlev and Gentofte University Hospital, the coordinating investigator (CI) will periodically review the accumulating data and, together with the research team, determine if a trial should be modified or discontinued. The CI will report to the ethical committee within 90 days of study termination or completion. As the risk profile of this trial is predicted to be minimal, a formal data monitoring committee has not been established.

### Adverse event reporting and harms {22}

#### Adverse events definition

##### AEs

An AE is any untoward medical occurrence in a patient or to whom a medical product or surgical procedure has been administered, including occurrences that are not necessarily caused by or related to the procedure. The study compares two acknowledged treatments with a known spectrum of side effects. Therefore, the assessment of AEs is not based on spontaneous reporting but on these specific expected AEs occurring from the procedure until the first follow-up (0–3 months). The most common side effects of TUMT include urinary tract infection (0–30% [37]), urinary retention (0–12% [38]), dysuria (0–6.7% [14]), post-procedure haematuria (0–26.8% [14]), haematuria requiring additional treatment (0–1.24% [14]), retrograde ejaculation (0–22.2% [12]), and ED (0–9% [37]). Compared to TURP, men undergoing TUMT are significantly less likely to require blood transfusion and experience retrograde ejaculation [12]. The most common side effects of PAE include urinary tract infection (0–13.8% [39]), late acute urinary retention (0–10% [40]), PES (0–100% [39]), access-site hematoma (2–12% [41]), pseudoaneurysm (0.5 to 6.3% [42]), and ED (0–2% [7]). Major complications following PAE such as non-target embolisation and vessel injury with subsequent bleeding are rare with an overall incidence of 0.5% [43]. Surgical complications will be registered in REDCap by the study personnel and classified using the Clavien-Dindo classification [29].

##### SAEs

A SAE is an AE or adverse reaction that results in death, is life-threatening, requires hospitalisation or prolonged existing hospitalisation, or results in persistent or significant disability or incapacity. SAEs during the study (0–3 months from the procedure) are reported on a specific SAE Case Report form in REDCap. Patient register information from inpatient care will be used to assess the frequency, duration, and cause of hospitalisation. Each SAE will be classified by the research physician according to intensity as mild, moderate, or severe. It will be classified as mild when the SAE is acceptable, the subject is aware of symptoms or signs, but they are easily tolerated. As moderate when it is disturbing and causes discomfort enough to interfere with usual daily activity. And as severe when it is unacceptable, the subject is incapable of working or doing usual daily activities. SAEs will also be classified by their likelihood of a causal relation with the given per-protocol procedure. In an unlikely causality, the event is most likely related to an aetiology other than the treatment under study. In a possible causality, a causal relationship is conceivable and cannot be dismissed. In a probable causality, there is good reason and sufficient documentation to assume a causal relationship.

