The secondary outcomes include the following:The mean IPSS of the two arms at all other follow-up occasions than the primary outcome.The mean procedure time for the conduction of TUMT and PAE as well as the calculated necrosis.Health-related quality of life measured by the mean IPSS-QoL, BII, and EQ-5D-5L. IPSS-QoL assesses the quality of life associated with symptoms from urinary problems. The BII is a self-reported, validated, disease-specific instrument for quantifying the interference of LUTS on the patient’s mental health and activity. As a measure of QoL, it is used to determine treatment outcomes in men with symptomatic benign prostatic hyperplasia [22]. The EQ-5D is the most widely applied instrument for health-economic assessment worldwide. Its index values are used in the estimation of quality-adjusted life year gains in economic evaluations of healthcare interventions [23].Mean satisfaction with treatment by a five-level bipolar Likert scale.Erectile function measured by the mean IIEF-EF score. The IIEF-EF domain score is a PROM used to measure erectile performance and assess disease severity in efficacy trials. It distinguishes between men with and without erectile dysfunction (ED), classifies levels of ED severity, and has the requisites to detect treatment-related changes in patients with ED [24, 25].Ejaculatory function measured by the mean DAN-PSS-1-sex. The DAN-PSS-1-sex is a validated instrument to determine erectile and ejaculatory function and its impact on the well-being of the patient [26].Incontinence measured by the mean ICIQ-UI-SF. The ICIQ-UI-SF is validated for evaluation of the frequency, severity, and impact on QoL of urinary incontinence [27].Mean prostate volume (PV) measured by TRUS in mL.Mean uroflowmetry outcomes of the two arms. We will be looking at voided volume, Qmax, and residual urine. Uroflowmetry is a non-invasive procedure used to measure the flow of urine throughout micturition. It provides useful information about the total voiding function and is used for diagnosis of lower urinary tract dysfunctions and evaluation of treatment response. Qmax is the value of the highest flow rate measured during the test; it will be set to zero if the patient has an indwelling catheter. Transabdominal ultrasound will be used to assess post-voided residual urine as it is accurate and non-invasive [28].Post-procedure catheterisation events, including the placement of an indwelling urinary catheter and the use of intermittent catheterisation. Catheterisation will be expressed as the reason for placement, duration, and frequency (in case of intermittent catheterisation). If an indwelling catheter is placed after the procedure, the post-procedure duration of catheterisation will be defined as days from the procedure till indwelling catheter cessation. Catheterisation for any other reason during the follow-up period will also be evaluated.Prostate-specific antigen (PSA) and creatinine. The absolute value of serum PSA (ng/mL) has a good predictive value for the determination of prostate volume. Continued PSA measurements assist in the detection of any de novo prostate cancer or progression of patients in active surveillance or watchful waiting. A rise in serum creatinine can be a result of BPH with urinary retention. Serum creatinine aids in the identification of any affection of the kidney from the procedures.De novo use of pharmacological LUTS treatment and surgical re-treatment rates will be collected from the patient’s health record.Incidence at 3 months post-procedure of urinary tract infection, acute urinary retention, dysuria, haematuria, post-embolisation syndrome (PES), hospital admission, and hospitalisation time. PES is defined as occurring within 48 h after surgery and consisting of influenza-like symptoms, pelvic pain, nausea, dysuria, or transient worsening of LUTS. Data on AEs and side effects will be collected from the patient’s health record and the follow-up visit at 3 months. Surgical complications will be categorised following the Clavien-Dindo grading [29].

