### Interim analyses {21b}

The trial will be conducted as a traditional fixed-sample design. An interim analysis of the safety of both procedures will be performed for every 50 cases at 6-month follow-up. The trial-initiating group will have access to the interim results and make the final decision if the trial is to be terminated.

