#### Adverse event reporting

The REDCap alerts tool will be used to notify the PI when an SAE has been reported in the database. The PI at each centre is responsible for reporting any unexpected SAEs to the ethics committee within 7 days. This report will be accompanied by remarks on any consequences of the trial. Throughout the total study duration, it is also the PIs responsibility to submit annual safety reports to the ethics committee of all serious expected and unexpected side effects and all serious events that have occurred during the period. This report will include an evaluation of the safety of the trial participants. The PI will keep study personnel informed of any safety issues that arise during the trial.

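### Systematic recording of serious adverse events stops at 3 months, yet the plan promises annual reports of all serious events for the whole study and a 5-year comparison of side effects

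*Protocol article*

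**What the plan says.** **What is collected.** The SAEs section states: "SAEs during the study (0–3 months from the procedure) are reported on a specific SAE Case Report form in REDCap". It then asks the research physician to classify each SAE by intensity and by likelihood of a causal link to the procedure. For non-serious events, the AEs section says that "the assessment of AEs is not based on spontaneous reporting but on these specific expected AEs", over the same three months. Table 1 marks the AEs/SAEs row once, at the 3-month visit. The Outcomes section names the harms to be compared: "Incidence at 3 months post-procedure of urinary tract infection, acute urinary retention, dysuria, haematuria, post-embolisation syndrome (PES), hospital admission, and hospitalisation time".

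**What is promised.** The Adverse event reporting section says: "Throughout the total study duration, it is also the PIs responsibility to submit annual safety reports to the ethics committee". The content is to be "all serious expected and unexpected side effects and all serious events that have occurred during the period". The Recruitment section puts the total duration at 8 years. The Objectives section lists the incidence of side effects among the items to be compared between arms over the five years after treatment.

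**The concern.** The recording rules and the reporting duties do not share a time frame. If sites follow the plan as written, no SAE form is due after month 3, while the principal investigators must keep reporting all serious events each year. The alert to the principal investigator depends on an SAE being entered in the database, so after month 3 that route has no described input either.

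Two things are at stake. Annual reports for later years may look complete while resting on whatever happens to be noticed. And the side-effect comparison, which is meant to inform patient counselling on durability and harm, would have defined incidence data for three months only.

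A smaller mismatch concerns the harm list. The AEs section names access-site haematoma and pseudoaneurysm among the common side effects of PAE, and non-target embolisation as a major complication. None of the three is named in the incidence outcome.

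**Working it through.** **1. Is the 3-month limit firm?** Four places agree. The SAEs section gives 0–3 months. The AEs section refers to "these specific expected AEs occurring from the procedure until the first follow-up (0–3 months"). The Outcomes section measures incidence at 3 months. Table 1 has one mark, at 3 months. Three of the four are in running text, so the reading does not depend on how the table was extracted. There is a related slip: the AEs section treats 3 months as the first follow-up, whereas Table 1 places FU 1 at 1 month.

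**2. Time frames side by side.**

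| Item | Section | Time frame |
|---|---|---|
| SAE form, with intensity and causality | SAEs | 0–3 months |
| Expected AEs | AEs | 0–3 months |
| Named harm incidence | Outcomes {12} | 3 months |
| Annual reports of all serious events | Adverse event reporting | whole study, 8 years |
| Comparison of side effects | Objectives {7} | 5 years |

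The last two rows cannot be filled from the first three.

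**3. Share of follow-up covered.** Inputs: a 3-month window, 5 years (60 months) of follow-up, and 223 patients. The planned number reproduces: 200 / (1 − 0.10) = 222.2, rounded up to 223.

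- Per patient: 3 / 60 = 0.05, or 5%.
- Total follow-up if all complete 5 years: 223 × 5 = 1,115 patient-years.
- Covered by the form: 223 × 0.25 = 55.75, about 56 patient-years.
- Not covered: 223 × 4.75 = 1,059.25, about 1,059 patient-years.

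**4. Calendar consequence.** Trial status gives the end of enrolment as December 2025 and the end of the study as December 2030. Table 1 allows screening, which includes randomisation, up to 365 days before the procedure.

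- If the last man is treated at once, the last SAE window closes in about March 2026. That leaves 57 months to December 2030.
- If he is treated a full year later, it closes in about March 2027. That leaves 45 months.

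So for the last 45 to 57 months no patient has an open SAE window. Since 45 / 12 = 3.75, at least three full yearly reporting periods have no SAE form behind them.

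**5. What continues after month 3.** From Table 1, Outcomes and Follow-up management:

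- catheter use, creatinine, PSA, uroflowmetry and prostate volume at 6, 12 and 24 months;
- questionnaires, including erectile function and incontinence, to 5 years;
- re-treatment at 1, 2 and 5 years;
- health-record assessment at 5 years.

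The SAEs section also uses inpatient register data on hospitalisation, with no separate end date. None of these sources is described as feeding the SAE form or its intensity and causality classification.

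**6. Harm lists compared.** Of the PAE side effects named in the AEs section, infection, retention and post-embolisation syndrome appear in the Outcomes incidence list, and erectile dysfunction has its own questionnaire outcome. Access-site haematoma (cited at 2–12%), pseudoaneurysm (0.5–6.3%) and non-target embolisation have no named outcome.

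**The case against.** The best defence is that harm capture does not end with the SAE form. The sources in step 5 run for two to five years, and creatinine is given an explicit role in detecting kidney effects. The article also condenses a full protocol that may name a later SAE source. The five-year wording in the Objectives governs a long list, some of which Table 1 collects only to two years, so it may be loosely meant. Neither the primary outcome nor early safety reporting is affected. All of this limits the point but does not remove it: the article's own statements about window, reports and objective still conflict.

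Three stronger readings are tempting, and the documents do not support them.

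- **That harms after month 3 go unseen.** They do not, for the reasons just given. What is missing is systematic SAE recording with grading.
- **That the safety interim contradicts the window or delays safety action.** The plan says "An interim analysis of the safety of both procedures will be performed for every 50 cases at 6-month follow-up". By 6 months the 0–3 month data are complete, and creatinine, catheter and questionnaire data from the 6-month visit are added. SAE alerts, reports of unexpected SAEs to the ethics committee within 7 days, and the coordinating investigator's periodic review all run independently of the interim.
- **That access-site harms of PAE are lost.** Haematoma and pseudoaneurysm are among the expected events assessed to 3 months, and surgical complications are registered and graded by Clavien-Dindo. They are recorded but not named as comparison outcomes.

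**Conclusion.** The point holds in this form: AE and SAE recording ends at 3 months, while the plan commits to annual reports of all serious events for the whole study and to a 5-year comparison of side effects. As the article stands, those two commitments have no systematic SAE data after month 3.

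The SAE form covers 5% of each patient's planned follow-up. The patient-year figures assume that all 223 men complete five years; deaths and dropout would reduce the total and change the share somewhat. The calendar figures assume the dates in Trial status are kept. The 5% describes one form, not all harm data. The conclusion also rests on the article alone, without the full protocol.

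The harm-list mismatch is a secondary matter of naming. Sample size, primary analysis and interim timing are not in question.

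**What to change.** State one SAE window and one data source, and use them consistently in Objectives, Outcomes, Table 1, AEs, SAEs and Adverse event reporting. There are two ways to do this:

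- **Extend collection.** Record SAEs, with intensity and causality, at the existing 6-, 12- and 24-month visits and at the 5-year record review. The annual reports and the 5-year objective then have data.
- **Restrict the claims.** If collection stays at 3 months, limit the annual reports and the side-effect objective to what is collected, and say so.

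In the same amendment, align the harms named under Outcomes with those in the AEs section. Name access-site haematoma and pseudoaneurysm, which are already assessed, and non-target embolisation, which that section calls a major complication. Correct the description of 3 months as the first follow-up.

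The cost is a short amendment and, under the first option, some extra data entry at sites. No new visits are needed and the sample size does not change.

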### Criteria for discontinuing or modifying allocated interventions {11b}

The patient can withdraw the informed consent and leave the study at any time without explanation. If the patient withdraws consent, no further data will be collected. The data already collected until that point will be stored and used for study purposes. If the patient requests to change the treatment option after randomisation, he will be referred to his respective department of urology for his preferred treatment option and included in the analysis as intention-to-treat. The study can be closed prematurely if any untoward patient complication is observed in either treatment arm, defined as serious adverse events (SAEs) resulting in organ failure or death.

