### Methods in analysis to handle protocol non-adherence and any statistical methods to handle missing data {20c}

The study is analysed as intention-to-treat. As data is expected to be missing completely at random, missing data will be handled by pairwise deletion.

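### A blanket intention-to-treat rule with switching allowed would, read literally, count a switcher's harms and procedure data under the procedure he was assigned rather than the one he had

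*Protocol article*

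**What the plan says.** Four parts of the protocol article bear on this.

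- **Switching.** Under {11b}, a man who asks to change treatment after randomisation is not withdrawn: "he will be referred to his respective department of urology for his preferred treatment option and included in the analysis as intention-to-treat".
- **Analysis rule.** Section {20c} is general: "The study is analysed as intention-to-treat". Neither section sets harms or procedure-level outcomes apart, and the article names no as-treated set.
- **Outcomes and safety review.** These are worded by procedure. The secondary outcomes in {12} include "The mean procedure time for the conduction of TUMT and PAE as well as the calculated necrosis". The interim section {21b} says "An interim analysis of the safety of both procedures will be performed for every 50 cases at 6-month follow-up". In {22}, the windows for adverse events and serious adverse events both start at the procedure, not at randomisation.
- **SAE causality.** Under {22}, "SAEs will also be classified by their likelihood of a causal relation with the given per-protocol procedure". The phrase is not defined. The lowest category reads: "In an unlikely causality, the event is most likely related to an aetiology other than the treatment under study".

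The objectives in {7} say that the secondary comparison is meant as a reference for clinicians who counsel patients on the choice between these procedures.

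**The concern.** Intention-to-treat suits the effectiveness question. Complications, procedure time and calculated necrosis are different, because they belong to the procedure performed. If a man randomised to TUMT has PAE and develops an access-site haematoma, the general rule puts that event in the TUMT column, although TUMT involves no arterial access. His PAE procedure time would go into the TUMT mean. Neither figure then describes the procedure named at the head of the column.

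Some switching is plausible in this design:

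- The trial is open-label ({17a}).
- Preference for TUMT or PAE can be part of the route to eligibility ({10}).
- Table 1 places randomisation in a screening window that runs from a year to two days before the procedure.
- No adherence strategy is planned ({11c}).

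At stake is the usefulness of the harms comparison for counselling. Differences between the procedures shrink towards zero as switching rises, and events peculiar to one procedure appear under the other.

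**Working it through.** **Whether the primary analysis is touched.** The article gives no figure for switching or for the harms analysis. Its one relevant figure is the sample size in {14}: one-sided alpha 0.025, power 80%, margin 3, assumed difference 1, SD 5.

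- Normal approximation: n per arm = 2 × (1.960 + 0.842)² × 5² / (3 − 1)² ≈ 98.1, rounded up to 99.
- Exact noncentral t: power 0.7997 at 99 per arm and 0.8037 at 100 per arm, so 100 per arm.
- Dropout: 200 / 0.9 = 222.2, rounded up to 223.

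The stated 100 per arm and 223 in total are reproduced. Nothing in this point changes them.

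**Effect of tabulating harms by assignment.** Let s be the share of an arm that receives the other procedure. An arm's rate by assignment is then

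rate = (1 − s) × rate of assigned procedure + s × rate of other procedure.

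Inputs from {22}: access-site haematoma after PAE 2–12%; post-procedure haematuria after TUMT 0–26.8%. Assumptions:

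- s is 2%, 5%, 10% or 20%, because no switching share is given.
- Access-site haematoma after TUMT is 0, because there is no arterial access.
- Haematuria after PAE is 0, for illustration only, because the article gives no figure.

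*Access-site haematomas in the TUMT arm per 100 men, with switching from TUMT to PAE: 100 × s × (0.02 to 0.12).*

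| s | Events |
|---|---|
| 2% | 0.04–0.24 |
| 5% | 0.1–0.6 |
| 10% | 0.2–1.2 |
| 20% | 0.4–2.4 |

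*Difference that remains when both arms switch equally: true difference × (1 − 2s), at the upper end of each range.*

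| s | Haematoma, true 12 points | Haematuria, true 26.8 points |
|---|---|---|
| 2% | 11.5 | 25.7 |
| 5% | 10.8 | 24.1 |
| 10% | 9.6 | 21.4 |
| 20% | 7.2 | 16.1 |

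The second table is an upper-end illustration. The haematuria range starts at zero, and where the true difference is zero there is nothing to dilute.

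**The causality wording.** The SAE text uses two references: the given per-protocol procedure, then the treatment under study. The word given points to what was administered; per-protocol can be read as what was allocated. For a man who crosses between TUMT and PAE, both are treatments under study, so a PAE complication does not meet the definition of the unlikely category. The middle and upper categories ask only whether a causal link is conceivable or documented, and do not mention allocation. The wording is therefore ambiguous, but it does not shut such an event out.

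**The case against.** The best defence is that no sentence applies intention-to-treat to harms specifically. The safety text is written by procedure, and so is the procedure-time outcome. A safety analysis set is usually left to the statistical analysis plan, which is not at hand, so its absence from an article is no fault. All of this is fair, and it limits the point: harms are tied to the randomised arm only by inference from a general rule. What remains is that the general rule is stated, has no exception, and follows a clause that sends switchers into it. An analysis plan that took {20c} at its word would carry the mismatch forward.

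A reader might also infer that a switcher's complications cannot be classed as related to treatment, and that the safety interims are weakened as a result. The documents do not support this. The natural sense of given is administered, and the category definitions allow a TUMT/PAE switcher's event to be judged against what he received. The early-closure criterion in {11b} turns on organ failure or death, with no relatedness condition. The reporting duties in {22} cover unexpected SAEs and all serious events, again whatever the causality rating, and {21b} does not make the interim depend on it. One narrow gap remains: a man who chooses a non-study treatment would have no clear causality reference. The article lists such alternatives in {6b}, but does not say that switchers receive them.

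A further objection is that an as-received comparison gives up the protection of randomisation where switching is driven by the patient. That stands, and it is why the by-assignment table should be kept beside it.

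**Conclusion.** The point holds as a mismatch between a stated analysis rule and the outcomes it reaches. Followed literally, {11b} and {20c} place a switcher's adverse events, SAEs, Clavien-Dindo grades, procedure time and calculated necrosis under the randomised procedure. That does not fit the wording of {12} and {21b} or the counselling aim in {7}.

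The size is modest unless switching is common. At an assumed 10% it amounts to about 0.2–1.2 misplaced access-site haematomas per 100 TUMT men. If both arms switch at that rate, a true 12-point difference would show as 9.6 points. These figures rest on an assumed switching share and on literature ranges quoted in the article. The primary comparison is not affected. The causality phrase needs a minor clarification and is not evidence that related events would be missed.

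**What to change.** In {20c}, limit intention-to-treat to the effectiveness outcomes. State that adverse events, SAEs, Clavien-Dindo grades, procedure time and calculated necrosis are tabulated by the procedure actually received. Show men who received neither TUMT nor PAE separately, and give the by-assignment table alongside. Align the switching sentence in {11b} with this.

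As a minor clarification in the SAE section of {22}, replace the undefined reference procedure with the procedure actually received, and record that procedure on the SAE form.

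The cost is a few sentences and one form field. Table 1 already schedules collection of technical details of the procedure, so little new data is needed. The real drawback is that the as-received comparison is not strictly randomised. It should be labelled as such and read together with the by-assignment table.
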